## Background

In the United States (U.S.), members of racial and ethnic minority groups are disproportionally affected by type 2 diabetes (T2D). For example, the prevalence of both diagnosed and undiagnosed T2D is nearly twice as high among Mexican-origin Hispanic/Latino adults compared to non-Hispanic Whites [1]. Furthermore, the American Heart Association has reported that only 14% of adult Hispanic/Latino Americans meet the criteria for “ideal cardiovascular health” as compared to 20% for non-Hispanic/Latino White Americans [2]. Rates of diabetes-related complications including premature death from diabetes, acute stroke and end-stage renal disease are also higher among Hispanic/Latino adults compared to their non-Hispanic/Latino White counterparts [3].

Beyond genetics and biological factors, such as achieved hemoglobin A1_c_ (HbA_1c_) levels, lipids, obesity and blood pressure, it is now recognized increasingly that sociocultural influences are also important factors in determining an individual’s risk related to the development of T2D and the associated complications. These influences include ethnicity (e.g., Mexican-Americans have a greater diabetes burden than Cuban-Americans); duration and impact of acculturation (the process by which immigrants adopt the attitudes, values, customs, beliefs, and behaviors of a new culture); place of residence; achieved education level; and economic status [4, 5]. Compounding this burden, Hispanic/Latinos are also a minority among diabetes care providers, researchers, or research participants. For example, Hispanic/Latinos represent just 1% of clinical trial participants, and Hispanic/Latinos are a small fraction of providers (e.g., Hispanic/Latinos are about 40% of California’s population but only 8% of nurses and 5% of doctors) [6, 7]. Therefore, given the previous lack of Hispanic/Latino participation in clinical research, this study aims to (a) find novel approaches to engage this population and (b) consider psychological, behavioral and environmental factors, as well as the traditional biological and genetic influences on the risk of progression of T2D in this growing but underserved U.S. population, as these have not be undertaken previously.

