### Aims

*The primary objective of this study is to determine the influence of the 5 major determinants of human health (genetics, biology, behavior, psychology, society/environment) on the real-world burden of T2D for Latino families.* To achieve this objective, beginning February 2019, Mil Familias (www.milfamilias.sansum.org/) began the establishment of an observational cohort of 1000 Latino families with at least one family member currently living with T2D, among whom we are studying the impact over time of the 5 main determinants of human health. We work with specially trained, bilingual Latino/a community health workers (known as Especialistas) who recruit participant families, conduct research activities including data collection, and, when necessary, refer families to appropriate community resources. Facilitated by these Especialistas, each individual family member contributes data annually on over 100 different variables relating to their genetics, biology, psychology, behavior, and society/environment, creating a Latino-focused biobank (“Living Information Bank”). Once the cohort is established, data analyses will inform the development of evidence-based, collaborative, and culturally-relevant prevention and treatment strategies.

An operational pilot involving over 100 adult Latino individuals with T2D, completed in 2018, established the feasibility of methods and created the infrastructure to scale to the 1000-family cohort (Mil Familias-Santa Barbara’s Operational Pilot to Understand Diabetes in the Latino Community NCT03736486).

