#### Data analysis

Statistical analyses will be performed in collaboration with SDRI’s data partner, Santa Barbara Actuaries, Inc. All statistics will be considered significant with *p* values < 0.05. Chi squared tests will be conducted to detect differences in categorical outcomes. T-tests will be conducted to test differences in continuous outcomes where the sample size is less than 50 for any sub population. Z tests will be conducted for continuous variables with a sample size greater than 50 where there is no evidence of violation of normality. For continuous outcomes that may violate the normality assumption, a log-normal transformation or other appropriate analysis may be applied.

In addition, independent variables may be confounders of each other’s effect on the outcomes and thus consideration will be given to explore likely confounders. There are adjustment approaches, such as propensity score matched cohorts, to address such biases. Regression analysis for a particular outcome can also be performed on various individual characteristics.

Based on the experience from the Operational Pilot, we expect the sample size of the full study to be sufficient to provide substantial levels of statistical significance to compare the relationship between outcomes and individual variables. For example, based on the Operational Pilot (*n* = 107), HbA_1c_ can be stratified into 2 groups (> 9 and < 7%). In the Pilot, we found that 40% had an HbA_1c_ < 7%, and for 28% it was > 9%. This was significant at the 3% level and this will fall below 1% with 160 participants and below 0.1% at 280. Our full study population is designed to have 1000 members, so we believe that the majority of individual variables of interest will be powered to show statistically significant conclusions.

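### The plan commits only to group-comparison tests and leaves regression optional, although many determinants and outcomes are continuous or ordered

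*Protocol article*

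**What the plan says.** The Aims section of the protocol article sets the task: "The primary objective of this study is to determine the influence of the 5 major determinants of human health" on the burden of type 2 diabetes in Latino families.

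The Data analysis section then commits to three procedures:

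- Categorical outcomes: "Chi squared tests will be conducted to detect differences in categorical outcomes".
- Continuous outcomes, smaller samples: "T-tests will be conducted to test differences in continuous outcomes where the sample size is less than 50 for any sub population".
- Continuous variables, larger samples: "Z tests will be conducted for continuous variables with a sample size greater than 50 where there is no evidence of violation of normality".

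The significance rule is "All statistics will be considered significant with *p* values < 0.05". Regression has a different status: "Regression analysis for a particular outcome can also be performed on various individual characteristics". The section's one example of grouping is an outcome: "HbA_1c_ can be stratified into 2 groups (> 9 and < 7"%).

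Tables 1 and 2 list many determinants that are scores, counts, readings or ordered items. They include the SF-12, adverse childhood events, PHQ-9, PSS-4, device-recorded sleep and activity, tortilla counts, income, education, the acculturation scale and the food security module. The Background names "achieved education level; and economic status" among the influences of interest. Several of the major secondary outcomes (HbA1c, blood pressure, waist circumference) are also continuous.

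**The concern.** Chi-squared, t and Z tests answer whether groups differ. The objective asks how an outcome varies with a determinant. When both are continuous, say HbA1c and a PHQ-9 score, none of the committed tests applies until one of them has been cut. When the determinant is ordered, such as education level, a standard chi-squared test gives the same result however the levels are arranged.

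Two things are at stake. The first is power, because cutting or ignoring order discards information that has been collected. The second is the cut-point: none is stated for any determinant, so it becomes a choice that can be made after seeing the data. Regression on the measured scale avoids both, and it is the one named method that the plan does not commit to.

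This point is separate from adjustment for confounding, and from whether the HbA1c thresholds in the sizing example are well chosen.

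**Working it through.** **The plan's own figure.** There is none for this question. The significance levels that the Data analysis section quotes for 40% versus 28% in the pilot concern something else and are not used here.

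**Inputs.** From the Data analysis section: significance level 0.05, the pilot proportions 40% and 28%, and a study size of 1000 members. Assumed, because the article does not state them: two-sided testing, 80% power as the reference, a normally distributed variable, a linear effect that is small, and independent participants.

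**1. Reference.** A 1-df test on the measured scale with 80% power has noncentrality (1.960 + 0.8416)² = 2.8016² = 7.849.

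**2. A determinant cut in two.** With a proportion p below the cut c, the information kept is E = φ(c)² / [p(1 − p)]. Power is then Φ(2.8016·√E − 1.960).

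| Cut | E | Loss | Power |
|---|---|---|---|
| Median | 0.3989² / 0.25 = 0.637 (= 2/π) | 36% | 61% |
| 75th percentile | 0.3178² / 0.1875 = 0.539 | 46% | 54% |
| 90th percentile | 0.1755² / 0.09 = 0.342 | 66% | 37% |

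**3. A determinant cut into more groups, tested as unordered.** The between-group share of variance rises, but so do the degrees of freedom. The noncentrality needed for 80% power is 9.635 on 2 df, 10.903 on 3 df and 11.935 on 4 df.

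- Tertiles: 0.793 × 7.849 / 9.635 = 0.646, a loss of 35%.
- Quartiles: 0.861 × 7.849 / 10.903 = 0.620, a loss of 38%.
- Quintiles: 0.897 × 7.849 / 11.935 = 0.590, a loss of 41%.

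Finer grouping therefore does not rescue an unordered test. The same groups scored in order would lose 21%, 14% and 10%.

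**4. A determinant that is already ordered, tested as unordered instead of by a 1-df trend.**

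- 3 levels: 1 − 7.849 / 9.635 = 19%.
- 4 levels: 1 − 7.849 / 10.903 = 28%.
- 5 levels: 1 − 7.849 / 11.935 = 34%.

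For a trend that the 1-df test detects with 80% power, the unordered test has 70.9%, 64.5% and 59.5% power (2, 3 and 4 df), and 52.1% on 6 df.

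**5. The outcome cut instead.** Suppose a continuous determinant is compared between the HbA1c groups of 40% and 28%, with HbA1c taken as normal. The mean of the lowest 40% is −0.966 and that of the highest 28% is 1.202. The information kept is (1.202 + 0.966)² / (1/0.40 + 1/0.28) = 4.70 / 6.07 = 0.774, a loss of 23%. The middle 32% of participants enter neither group.

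**6. In terms of sample size.** For a correlation of 0.10, 80% power needs 7.849 / 0.01, or 785 people, on the measured scale, and 785 / 0.637, or about 1233, after a median split. At 1000 participants the smallest correlation detectable with 80% power is √(7.849 / 1000) = 0.089. After a median split it is √(7.849 / 637) = 0.111.

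**The case against.** The strongest reply is that the article never says that a determinant will be cut. It gives no determinant cut-point, and its one grouping example divides HbA1c, a listed secondary outcome. The Z-test sentence speaks of continuous variables, not outcomes. Scores and device readings could therefore be compared on their measured scale between HbA1c groups or between participants with and without diabetes. This stands. A reader might infer that the plan uses determinants only as unordered groups and so loses about a third of their information throughout; the text does not support that. The loss does not vanish under the other reading, though. Where the outcome is continuous it moves to the outcome, at about 23% for the HbA1c groups. Where the grouping is a real category such as diabetes status, there is no loss from cutting.

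Further replies, and what remains of them:

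- A linear-by-linear test is itself a chi-squared test, so the phrase does not strictly exclude trend versions. True, but none is named, and the standard test ignores order.
- Regression is permitted, and model detail belongs in a full protocol or analysis plan that is not shown. The detail is rightly left there. The ranking of methods is not left open, because the article says which tests will be done and makes regression an addition.
- A reader might conclude that dose-response cannot be seen. That goes too far: optional regression could show it, and so could ordered group means.
- The shift from 0.089 to 0.111 is modest, and the cohort may reach 6000 individuals. The absolute gap then shrinks, but the ratio of √(π/2) = 1.25 stays.
- Tables 1 and 2 also hold many yes/no or nominal items, such as country of birth, insurance type and retinopathy. Group tests suit these, and no claim is made here about the share of variables affected.

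**Conclusion.** The concern holds in limited form. The committed tests compare groups, the method that fits the objective is optional, and relating a continuous determinant to a continuous outcome under the committed tests requires cutting one of them. This rests on the article's wording, not on a silence.

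The size is conditional and should be given as a range. It runs from about 19% (a 3-level ordered item tested as unordered) to about 66% (a 90/10 split), with 36% for a median split and 23% for the HbA1c extreme groups. These figures assume normality, a linear effect, two-sided 0.05, 80% power and independent participants; family clustering is ignored. The loss is a risk of following the committed plan, not a certainty.

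The declared primary outcome, establishing the cohort, does not depend on these tests. The change is one that should be made for the sake of the determinant objective; it does not threaten the study.

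**What to change.** In Data analysis, state that regression will be the main analysis of the relation between determinants and outcomes, as follows:

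- Continuous determinants and continuous outcomes stay on their measured scale, with a spline term as a check for curvature.
- Ordered determinants are tested by a 1-df trend.
- Ordered outcomes are analysed by proportional odds or a linear-by-linear test.
- Chi-squared, t and Z tests are kept for genuinely unordered groups, such as country of birth or insurance type.

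The cost is a change of wording and slightly more analysis work, with no new data, visits or participants. A linear term can miss a non-monotone relation, which the spline check is there to catch.

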### Quality control of data collection

In concordance with the Mil Familias Operational Pilot Study, standard operating procedures (SOPs) are developed or adapted and followed to ensure standardized implementation of the study protocol. In addition, training modules for the Especialistas and other study staff are created and implemented using structured templates. More specifically, these trainings focus on (but are not limited to): recruitment, Good Clinical Practice (GCP), T2D knowledge, care navigation, data collection and management. Further, a mandatory three-person data verification check is in place from the initial data collection through final data input into a secure electronic data capture system (REDCap EDC System). Given the high retention rate (over 85% of participants completed all study visits) and associated completeness of individual and aggregate datasets in the Mil Familias Operational Pilot Study, it is anticipated that this study will achieve similar sustained levels of data quantity and quality, contributing to its overall success.

## Discussion

Currently, Latinos bear an unacceptable excess and unfair burden of cardio-metabolic disease and the associated serious complications. This Cohort Establishment study will create a large observational cohort of 1000 Latino families impacted by T2D. Data collected from participant families will be used to create a unique, Latino-focused Living Information Bank which will help determine future effective evidence-based prevention and treatment intervention strategies that are equitable and culturally-relevant.

Public health programs have utilized community health workers (CHWs) with much success [37–40]. Growing research demonstrates the positive impact of CHW efforts and the significant cost savings they generate. Findings confirm that CHWs are highly effective at providing instruction on health care issues such as nutrition and physical activity, particularly for Latino patients who have diabetes, and this results in significantly improved diabetes control and health outcomes [41]. By using Especialistas in this study, we anticipate effective outreach, participation, and retention with our study participants.

Based on the success of the initial Mil Familias Operational Pilot study, we anticipate that the Cohort Establishment study will be completed in the proposed time period. The participating Latino families are given the opportunity to build trust-based relationships with their Especialistas who act as their personal health liaison and advocate throughout the study. Such an exchange of trust is vital to the data collection process as the aim is to create a safe-space in which participants feel comfortable to share private and personal information. The uniqueness of this study is centered on collecting comprehensive cross-sectional and longitudinal information from a traditionally hard-to-reach population.

### Limitations

While a potential limitation of this study is lack of an active control group, there are other cohorts of interest published elsewhere, including the Hispanic Community Health Study/Study of Latinos (HCHS/SOL). This is a community-based cohort study of 16,415 self-identified Hispanic/Latino adults of which 2148 individuals self-reported a diagnosis of diabetes [42]. Additionally, it is worth noting that the study population could be limited to individuals of Mexican heritage by excluding from analysis Latino individuals from other countries of origin, such as Panamanians, Hondurans, or Guatemalans.

By creating and providing the framework for the Cohort Establishment study, we intend to inform new approaches regarding equity and excellence in diabetes research and care. In taking a deeper look into the complex set of factors that contribute to the burden of diabetes in Latino families, we will assess if cardio-metabolic disease risks go beyond the traditional biological and genetic factors. In this pursuit, further investigation regarding the factors that affect the Latino population will help to determine and promote novel prevention and intervention strategies to reduce the burden of cardio-metabolic disease in this population. Breaking the code on the interplay of cardio-metabolic risk factors may very well help not only this fast growing segment of the U.S. population, but also other high-risk populations in the U.S. and around the globe.

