### Setting and participants

In Santa Barbara County, the population is 45.6% Latino, most of Mexican ancestry [8]. To establish the Mil Familias cohort, up to 1200 families may be screened and enrolled with an estimated 20% screen-fail or dropout rate, resulting in approximately 1000 families in the study. Potential participants are selected from Santa Barbara County and surrounding communities or satellite sites with the help of existing community allies and healthcare organizations. Approaches to recruitment include engagement with and referrals from: local Federally Qualified Health Centers (FQHCs); community service providers; academic institutions with high English as a Second Language enrollment (i.e., Hispanic Serving Institutions); local employers; local media (Spanish and English language); social media; advertisements; participation in community events; SDRI physical site and websites; and ad hoc interaction with Especialistas. This type of combined approach was successful in the operational pilot. Only participants who meet all eligibility criteria are enrolled and study staff confirm participant eligibility during the screening and enrollment encounter. A “family” is followed as one unit, but is estimated to include on average 3 to 5 individuals (based on findings from the operational pilot). Therefore, up to 6000 individuals may be screened and enrolled.

The definition of “Mil Familias family” accounts for statistical, tracking, and reporting requirements of this study and is based on the U.S. Census definition of a “family group” and modified to include single-person units and relatedness via domestic partnership [9]. Each individual may participate in just one Mil Familias family. A “Mil Familias family” consists of an enrolled individual family representative and any enrolled family members. The family representative is the first enrolled. A family member is any individual subsequently enrolled who: (a) resides with the family representative (i.e., co-resides) and (b) is an immediate relative (spouse/partner, parent, child, or sibling) to the family representative by birth, marriage/domestic partnership, or adoption.

**Inclusion Criteria** (family representative)

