Males or females ≥ 7 years of age at enrollment.Self-reported Hispanic/Latino heritage.Co-resides with immediate family member (as defined above) or self with established diagnosis of T2D.Signed and dated written informed consent by the date of enrollment.Based on the research staff’s judgment, participant or participant’s representative must have a good understanding, ability, and willingness to adhere to the protocol, including performance of self-monitored data collection during the wearable device portion of the study.

**Inclusion Criteria** (family member)
Males or females ≥ 7 years of age at enrollment.Self-reported Hispanic/Latino heritage.Co-resides with immediate family representative.Signed and dated written informed consent by the date of enrollment.Based on the research staff’s judgment, participant or participant’s representative must have a good understanding, ability, and willingness to adhere to the protocol, including performance of self-monitored data collection during the wearable device portion of the study.

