Email	Intro. Interview/Demographics/Contacts	Yes	Yes	–	–
Household size, income	Intro. Interview/Demographics	Yes	Yes	Par	Par
Education	Intro. Interview/Demographics	Yes	Yes	Par	Par
Insurance status	Intro. Interview/Demographics	Yes	Yes	Par	Par
Insurance type/payer	Intro. Interview/Demographics	Yes	Yes	Par	Par
Recent provider visit	Intro. Interview/Demographics	Yes	Yes	Par	Par
Country of birth	Intro. Interview/Demographics	Yes	Yes	Par	Par
Marital status	Intro. Interview/Demographics	Yes	Yes	–	–
Occupation	Intro. Interview/Demographics	Yes	Yes	–	–
Night shifts	Intro. Interview/Demographics	Yes	Yes	–	–
Alcohol, tobacco use	Intro. Interview/Demographics	Yes	Yes	–	–
Acculturation	BASH: Brief Acculturation Scale for Hispanics [29]	Yes	Yes	–	–
Introductory Interview					
DM cause	Intro. Interview: Why is DM common in Latino families?	Yes	Yes	–	–
DM prevention	Intro. Interview: What can prevent DM in Latino families?	Yes	Yes	–	–
DM challenges	Intro. Interview: What difficulties to get help with DM?	Yes	Yes	–	–
Health literacy	SAHL: Short Assessment of Health Literacy [30]	Yes	Yes	–	–
Health numeracy	NVS: Newest Vital Signs [31]	Yes	Yes	–	–
Trust in physician	TPS: Trust in Physician Scale [32]	Yes	Yes	–	–
Social needs stability	SNST: Health Leads Social Needs Screening Toolkit [33]	Yes	Yes	–	–
Food (In)security	FSSM: Food Security Survey Module [34]	Yes	Yes	–	–
Functional support	SSQ6: Social Support Questionnaire short version [35]	Yes	–	–	–
Support structure	mMOS-SSS: Modified Medical Outcomes Study Social Support Survey [36]	Yes	Yes	–	–

*Abbreviations*: *DM* Diabetes mellitus, *HbA*_*1c*_ Hemoglobin A_1c_, *Intro*., Introductory, *Opt* Optional, *Par* Participant

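### Households are selected through a member with T2D, so analyses pooling members with and without T2D tie prevalent T2D and HbA1c to household size by construction

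*Protocol article*

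**What the plan says.** - **Selection.** Under Aims, the cohort is "an observational cohort of 1000 Latino families with at least one family member currently living with T2D". The family representative must satisfy the criterion "Co-resides with immediate family member (as defined above) or self with established diagnosis of T2D". Co-resident immediate relatives may then enrol whether or not they have T2D; Participant Groups 2 and 4 are the members without it. Those groups are said to decide which data are collected. They are not described as analysis strata.
- **Family.** Under Setting and participants, a family "consists of an enrolled individual family representative and any enrolled family members", and the Census definition is "modified to include single-person units and relatedness via domestic partnership". A family "is estimated to include on average 3 to 5 individuals", so that "up to 6000 individuals may be screened and enrolled".
- **Variables.** HbA1c is a major secondary outcome. Table 1 has it collected in adults with and without T2D, and as optional in children. Table 2 lists "Household size, income" for all four groups.
- **Analysis.** The Data analysis section commits to chi-squared tests for categorical outcomes and t or z tests for continuous ones, at the 0.05 level. Regression and propensity matching are mentioned as possibilities, and confounding is to be considered. Household size and selection through a case are not mentioned.
- **Limitations.** The section states that "a potential limitation of this study is lack of an active control group" and refers to a published community cohort. It does not mention how families are selected.

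**The concern.** Prevalent T2D is part of the entry rule. A small household can enter only if a large fraction of it has T2D, while a large household can enter with a small fraction. Once members with and without T2D are pooled, the share with T2D declines with household size even when nothing influences T2D. Mean HbA1c follows, because it is higher in people with T2D.

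A determinant that varies with household size inherits this pattern. Under the listed tests it would appear to protect against or promote T2D, and the stated objective on the influence of society and environment would be answered in part by the sampling rule. Comparison with an outside cohort would not remove a distortion that lies within this cohort's own comparisons.

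**Working it through.** **1. The plan's own figure.** 1200 families × 5 members (upper end of the stated average of 3 to 5) = 6000, as stated. The plan thus expects several members per family, of whom the entry rule requires only one to have T2D.

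**2. Share with T2D by household size when nothing affects T2D.** Assumption, not in the documents: each person has T2D independently with probability p, from 0.10 to 0.30. A household of size k is selected if it holds at least one case, so the expected share is p / [1 − (1 − p)^k].

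| Size k | p = 0.10 | p = 0.30 |
|---|---|---|
| 1 | 100% | 100% |
| 2 | 0.10/0.190 = 53% | 0.30/0.510 = 59% |
| 3 | 0.10/0.271 = 37% | 0.30/0.657 = 46% |
| 5 | 0.10/0.410 = 24% | 0.30/0.832 = 36% |

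A second model, with one qualifying case and risk p in each other member, gives [1 + (k − 1)p]/k. At p = 0.15 this is 100%, 58%, 43%, 36% and 32% for sizes 1 to 5. Both models show the same decline.

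**3. Pooled mean HbA1c.** Assumed means are 7.9 with T2D and 5.5 without, so the pooled mean is 5.5 + 2.4 × share. At p = 0.2 the shares for sizes 1, 3 and 5 are 100%, 41.0% and 29.7%, giving 7.9, 6.5 and 6.2.

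**4. Effect on a null determinant.** Simulation of 1000 selected households, 150 runs per null setting, with family-cluster-robust standard errors, so clustering does not explain the result. Assumed: sizes 1 to 7, mean after selection 4.1 to 4.3, all household members enrol, p from 0.10 to 0.30.

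| Correlation with household size | Odds ratio for T2D per SD (true value 1) | Runs with p < 0.05 |
|---|---|---|
| 0 | 1.00 | 3-4% |
| 0.1 | about 0.97 | 19-44% |
| 0.3 | 0.89-0.92 | 93-100% |
| −0.3 | 1.09-1.12 | 93-100% |

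For pooled HbA1c at correlation 0.3, the slope was about −0.05 per SD and 57-87% of runs were significant.

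A separate simulation applied the chi-squared test that the plan names, under the second model, to a null binary determinant whose latent score correlated 0.2 to 0.4 with family size. It was significant in 42% to 99% of runs at p = 0.15 (28% to 100% over p = 0.10 to 0.20).

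**5. Which feature is responsible.** With single-person households removed (p = 0.2, correlation 0.3), the odds ratio was still 0.92 and 95% of runs were significant. The requirement of at least one case is enough.

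**6. What removes it.**
- Adjusting for household size (families of two or more) returned the null odds ratio to 1.00 and significance to 2-6%. In the run without single-person households it was 9%; simulation error is √(0.05 × 0.95/150) = 1.8 percentage points.
- HbA1c within members with T2D had a slope of about 0 and 3-9% significant.
- Leaving out the qualifying member brought the chi-squared test to about 2-8%. Under the model of step 2 at p = 0.15, leaving out one case gives a nearly flat share: (2 × 0.5405 − 1)/1 = 8.1% at size 2 and (5 × 0.2696 − 1)/4 = 8.7% at size 5.

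**7. True effects.** At p = 0.2, a true odds ratio of 1.5 per SD, uncorrelated with size, was estimated as 1.21 unadjusted and 1.20 adjusted for size. Size adjustment removes the false association but does not restore a true one.

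**The case against.** The strongest reply is that the article does not commit to the analysis that fails. T2D status is not a listed outcome. The only worked HbA1c example, in the Data analysis section, comes from a pilot of adults with T2D, and within T2D there is no artefact. Confounder adjustment is left open, household size is collected, and a fuller analysis plan may deal with this. The Limitations sentence is not false. Every input to the magnitude is assumed, and the odds ratios are small.

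Most of this stands as a limit on scope. It does not dispose of the point. The text names unadjusted tests as those to be carried out, makes HbA1c an outcome collected in adults of both kinds, does not make T2D status an analysis stratum, and sets an objective that invites the pooled comparison. Those tests, applied to the pooled cohort, would mislead.

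Four stronger readings are tempting and are not supported:
- A reader might infer that household determinants in general will show false effects. Only those correlated with household size do; at correlation 0 the error rate was nominal.
- A reader might blame single-person families. Step 5 shows that they are not the cause.
- A reader might infer that a single-person family must be the person with T2D. The family counts enrolled persons only, and the representative may qualify through a relative who is not stated to have to enrol. The exact tie is to the household, not to the enrolled family.
- A reader might conclude that the cohort cannot study household-level causes of T2D occurrence at all. New-onset diabetes is recorded prospectively, and the entry rule does not force incidence among members free of T2D at enrolment.

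**Conclusion.** The point holds in a limited form. It applies when the outcome is prevalent T2D, or HbA1c pooled over T2D status, and the determinant is correlated with household size: size itself, and plausibly income. There the listed unadjusted tests would report an association created by the entry rule. True household-level effects on prevalent T2D are attenuated as well, even after size adjustment.

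The direction of the artefact follows from the design. Its size does not: it rests on assumed T2D risk, household-size distribution, HbA1c means, full enrolment of households and, above all, the correlation with size. At correlation 0.1 the error rate is several times nominal; at 0.3 a false finding is nearly certain, though the odds ratio stays within about 12% of 1. HbA1c within T2D, incident T2D and the primary outcome of creating the cohort are unaffected in this way. This is a low-cost improvement to the plan, not a flaw in the cohort.

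**What to change.** In Data analysis:
- Analyse HbA1c and measures of severity separately in members with and without T2D.
- For any analysis of prevalent T2D, include household size as a covariate and condition on ascertainment, for example by leaving out one case per family under a pre-set rule such as the first-enrolled member with T2D. A fixed rule is needed because the representative may not have T2D and a family may hold several cases.
- For questions about the occurrence of T2D, use incident T2D among members free of it at enrolment.

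In Limitations, add that families are selected through a case; that associations of household-level determinants with prevalent T2D are therefore biased, by false associations through household size and by attenuation of true effects even after size adjustment; and that an external cohort does not remove this.

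The cost is wording only, since household size and new-onset diabetes are already collected. The downside is fewer T2D cases and less precision in the prevalent-T2D analysis.
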